### Time schedule of enrolment

As outlined in Figure 1, the intervention will be introduced over a 1-month period via formalised TTS and education on trauma admitting wards via key stakeholder engagement. In the Group 1 hospitals this will occur at the start of the trial. For the Group 2 hospitals, this introduction period will occur after the 12-month data collection period for routine care (Group 1: TTS implementation → TTS maintenance, Group 2: standard care → TTS implementation). Overall recruitment is expected to take approximately 24 months, which is the estimated time it will take to recruit 6,380 multi-trauma patients, with the final follow-up interviews scheduled at 36 months.

### Data collection

Data collection processes are the same for both Groups. The prospectively identified eligible patients will have their primary and secondary survey performed in the ED. All clinical reviews (including ward rounds) in the first 24 hours on the ward after surgical or interventional radiology intervention will be documented using a previously used [15,16] data collection tool (Additional file 2: Appendix B). Data will be collected by a trained research nurse will include demographic variables, mechanism of injury, Australasian Triage Scale category (ATS) [18] and Glasgow Coma Scale (GCS) on arrival in ED. The Injury Severity Score (ISS) [19] will be calculated after discharge. An ISS score of greater than 15 indicates severe trauma.

Data related to the inpatient admission will include whether a (formalised) TTS is documented during admission and which components of the TTS are performed. A list of injuries, newly detected injuries and changes in management will be collected. A central blinded panel of experts, comprised of at least two emergency physicians and 2 (trauma) surgeons, will class newly detected injuries in-hospital as Type I, Type II or not a new injury (see Table 2). A scripted follow-up telephone interview (Additional file 3: Appendix C) will be conducted at 1, 6 and 12 months after discharge. This follow-up interview will collect data on (Type III) missed injuries after discharge, complications of the injury (parasthaesia, chronic pain) or complications of care (postoperative infections and venous thrombo-embolism), return to pre-injury function, and a validated quality of life (QoL) questionnaire (EuroQoL EQ-5D-5 L [20]).

**Table 2 Tab2:** **Data Collection**

***Time***	***Data collection process***
Enrolment	A trained research assistant will prospectively review (electronic) medical records for details on all clinical examinations, pathology tests and diagnostic imaging performed in the first 24 hours of admission. A standardised data collection form will be used for all patients. This review will occur between 24 and 48 hours after initial admission. This data is routinely collected data and as such, patient will not be asked to consent to this.
Enrolment	The patient or proxy will be asked to consent for the follow-up at 1, 6 and 12 months. The patient or proxy will be asked to provide at least two contact numbers and will be informed on the detail of these follow up interviews.
Follow-up	Structured interview at 1, 6 and 12 months after hospital discharge. A list of self-reported missed injuries will be adjudicated by an expert panel to classify the in-hospital missed injury (none, Type I or II) and any Type III injury as definite or likely, as well as to determine clinical significance of any missed injury
Follow-up	A trained research assistant will conduct a scripted follow-up interview that will include questions on delayed diagnosis or missed injuries, level of functioning, time off work and quality of life
	*Study measurements*
	Age
	Sex
	Ethnicity
	Occupation
	ISS score.
	Length of Hospital stay, length of ICU stay
	TTS performance and components of TTS (Additional file 1: Appendix A)
	Diagnoses made after 24 hours in hospital, resultant management (active or conservative), diagnostic procedures or tests.
	Predefined complications of care: post-operative infection (wound infection, cathether-related urinary tract infection, pneumonia, sepsis), and venous thrombo-embolism (Deep Vein Thrombosis, Pulmonary embolism)
	Predefined complications of injury: (ongoing or chronic pain, parasthesia, post-concussion syndrome or symptoms)
	Numbers of CT, MRI and ultrasound scans performed
	Details of unplanned attendances and readmissions to hospital
	Patient quality of life at 1, 6, 12 months (EQ-5D-5 L)
	Proportion of usual days of work or study lost at 1, 6 and 12 months
	Missed injury after hospital discharge
	Medical and nursing time used to assess patients in the first 24 hours
	ICD-10 diagnostic and procedure codes
	Australian-Revised Diagnostic-Related Group (AR-DRG) codes
	Community medical services provided
	Primary resource use through Medicare Benefit Scheme (MBS) and the Pharmaceutical Benefit Scheme (PBS) for a 12-month period following the index hospitalizations

If not contactable during initial phone call, up to five attempts will be made. Patients can indicate during follow-up that an injury was missed during their hospital stay. These self-reported injuries will be checked against relevant medical records and imaging reports and defined by the expert panel as missed injury (definitely, likely, unlikely, unknown) or a complication of care or injury. An injury will only be classified as definite or likely (Type III) ‘missed injury’ if there is no evidence (in medical record or radiology report) of the self-reported injury during the hospital stay. The panel will determine the clinical significance of these injuries based on change in management and expected effect on (duration) of morbidity.

Patients who reported a missed injury will be offered appropriate pathways for follow-up. Finally, we will undertake a search of the Death Registry to identify the mortality rate at 12 months post hospital discharge and cause of death.

Appropriate data on the associated cost-implications will be collected during the trial in order to conduct a cost-effectiveness analysis. Items identified that require appropriate measurement and valuation include: medical and nursing time used to assess patients in the first 24 hours, requested advanced imaging type and frequency, ICU length of stay, hospital length of stay, ICD-10 diagnostic and procedure codes, Australian-Revised Diagnostic-Related Group (AR-DRG) codes, patient time-off work, community medical services provided, and re-admissions to hospital.

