### Aims and hypotheses

Our primary aim is to determine whether the implementation of a formalised TTS will decrease missed injuries post hospital discharge (Type III injuries) and, as secondary aim, increase injury detection in hospital (Type I and II injuries combined). We further hypothesise that the intervention effect will be maintained and that the intervention would lead to decreased clinically significant missed injuries as judged by a blinded expert panel, decreased hospital and ICU bed days, decreased readmissions to hospital, improved quality of life and decreased time off work. We expect complications of the injuries to be the same, but complications of care to be less. If no difference between injury rates is found, we hypothesise that both arms will be equivalent in resource utilisation (ICU and hospital bed days, investigations ordered, interventions required).

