### Outcome measures

The primary outcome is Type III missed (Post-hospital discharge) injury rate. This study aims to compare the effect of a formalised TTS compared to routine care on missed injury rates after hospital discharge (type III).

Secondary outcomes are:Maintenance of intervention effect (comparing two 12-month periods in Group 1)*During Hospital Stay*In-hospital missed injury rate (Type I and II combined)Proportion of TTS performedHospital bed days, ICU bed days*During Follow-up (1,6 and 12 months post hospital discharge)*Clinically significant missed injuries (as determined by expert panel)Interventions required for delayed diagnosis (Type I and II) or missed injuries (Type III)Diagnostic imaging usage (CT, MRI, USS)Predefined complications of care and injury (see above)Readmissions to hospitalDays off workQuality of life (EQ-5D-5 L)Days off workMortality

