### Statistical analysis and sample size

The primary analysis will be by intention-to-treat (ITT). Per-protocol analyses will also be performed, based on all patients completing 1, 6 and 12 months follow-up. Based on our prospective study [16], comparing routine care with the formalised TTS group, we anticipate a decrease in post discharge (Type III) injuries from 14% to 9%. We foresee this will be accompanied by an increase of in-hospital injury detection (missed injury Type I and II combined) from 4% to 9%.

The sample size for a cluster-randomized trial requires adjustment of the number of patients that a corresponding individually randomized trial would have needed. This is due to variation between the clusters, and results in a correction using the intra-cluster correlation coefficient (ICC) [21]. Using an alpha of 0.05 and a power of 0.80, a sample size of 638 patients per group, with 1-year follow-up completed, would be required if individually randomised. Our previous study [17] achieved a telephone follow-up rate of 40% at 6 months. Extrapolating a similar conservative follow-up rate at 12 months, a total of 3,190 patients will be required (1,595 for each cohort) to answer the primary hypothesis. To separately answer a before-and-after comparison in Group 2 hospitals a similar sample is required. This results in a sample of 6,380 patients, with complete 1-year follow-up in at least 2,552. Since approximately 0.4% [22] of all ED presentations consist of multi-trauma patients, approximately 1,600,000 ED presentations will be required. For an approximate 24-month recruitment period, this equates to 16 hospitals that have an average annual census of 50,000 presentations. Based on this sample size, the maximum ICC that can be present before the power of the study is reduced below 80% is dependent on cluster size and numbers and presented in Table 3*.*

**Table 3 Tab3:** **Approximate maximum intra-class correlation (ICC) for various cluster sizes and number of intervention hospitals to answer primary hypothesis**

**Number of intervention (and control) hospitals**	**Average size of cluster**	**Maximum ICC to have 80% power to detect 5% difference**
8	400	0.01
15	400	0.02
21	400	0.03
9	300	0.01
15	300	0.02
22	300	0.03
10	200	0.01
16	200	0.02
23	200	0.03

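### Mortality is timed from hospital discharge, so on the natural reading deaths in hospital after enrolment are not counted and the clock starts at an event the intervention may move

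*Protocol article*

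**What the plan says.** In the Data collection section, in the text after Table 2, the protocol article states that "we will undertake a search of the Death Registry to identify the mortality rate at 12 months post hospital discharge and cause of death".

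Under Outcome measures, the secondary outcomes fall into two timed groups. Mortality closes the group headed "During Follow-up (1,6 and 12 months post hospital discharge". The group for the hospital stay holds the in-hospital missed injury rate and then "Proportion of TTS performedHospital bed days, ICU bed days". It contains no death outcome.

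Three other statements bear on the point:

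- **Entry.** Under Inclusion criteria, patients must be admitted for at least 24 hours. The Intervention section requires the survey form within 24 hours of admission.
- **Expected effect.** Aims and hypotheses lists among the expected benefits "decreased hospital and ICU bed days, decreased readmissions to hospital, improved quality of life and decreased time off work".
- **Population.** Statistical analysis and sample size states: "The primary analysis will be by intention-to-treat (ITT").

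**The concern.** Hospitals are randomised before any patient is admitted, and patients enter the study at about 24 hours of admission. Everything the survey might do to survival in hospital happens between that point and discharge. A mortality outcome whose clock starts at discharge does not naturally cover this interval.

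Two things are at stake.

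1. **Omitted deaths.** A patient who is enrolled and dies in hospital never has a discharge alive from which to count 12 months. The Background says clinically significant missed injuries are more likely to lead to prolonged morbidity or mortality. Deaths before discharge are among those an in-hospital re-examination could influence.
2. **A time origin that depends on treatment.** The protocol expects the survey to reduce bed days. If it does, the start of follow-up for death moves earlier in the intervention arm. The arms would then be compared over different stretches of time since injury, and among patients selected by having survived to discharge.

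**Working it through.** **Inputs.** From the protocol article: 14% versus 9% for the primary outcome, alpha 0.05, power 0.80, 638 per group, 40% telephone follow-up, and 1,595 recruited per cohort for the primary comparison. The article gives no mortality figure, so every death rate below is an assumption.

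**Step 1: the plan's own figure.** The two-sided test of two proportions with pooled variance and no continuity correction has mean proportion (0.14 + 0.09)/2 = 0.115:

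n = [1.960 × √(2 × 0.115 × 0.885) + 0.8416 × √(0.14 × 0.86 + 0.09 × 0.91)]² / 0.05²
= [0.8843 + 0.3785]² / 0.0025 = about 637.9, which rounds up to 638.

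Then 638 / 0.40 = 1,595 per cohort, and 2 × 1,595 = 3,190. The figures reproduce. None of them uses mortality, so nothing below alters them.

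**Step 2: deaths outside the window.** Let L be the length of stay in days and t the day of death after admission. Counting from discharge, a death enters the outcome only if L < t ≤ L + 365. A death during the stay does not qualify. If a proportion h of enrolled patients die in hospital, the number omitted per 1,595 is 1,595 × h:

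| Assumed h | Calculation | Deaths omitted |
|---|---|---|
| 0.5% | 1,595 × 0.005 = 7.98 | about 8 |
| 1% | 1,595 × 0.01 = 15.95 | about 16 |
| 3% | 1,595 × 0.03 = 47.85 | about 48 |

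These are deaths missing from one arm, not a difference between arms. The documents offer no basis for estimating the between-arm distortion.

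**Step 3: share of all deaths.** With d the risk of death in the 12 months after discharge among those discharged alive, total risk is h + (1 − h)d, and the omitted share is h / [h + (1 − h)d].

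- h = 0.5%, d = 5%: 0.005 / (0.005 + 0.995 × 0.05) = 0.005 / 0.05475 = 9%.
- h = 3%, d = 1%: 0.03 / (0.03 + 0.97 × 0.01) = 0.03 / 0.0397 = 76%.

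The share is very sensitive to the two assumed rates. The range shows only that the omission could be small or could be most of the deaths.

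**Step 4: effect of a shorter stay.** Take two patients who die on the same day after admission, day 10. One was discharged on day 9, the other was still an inpatient. Under the rule in Step 2 the first death counts (9 < 10) and the second does not. An intervention that changes only the discharge date can therefore change which deaths are counted.

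**Step 5: the benign reading.** Suppose the phrase fixes only the end of the registry search and all earlier deaths count. Survivors to discharge are then followed for L + 365 days from admission, so the horizon varies with length of stay. For a patient who dies in hospital, the stated horizon has no starting date.

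**The case against.** The strongest reply is that exclusion is inferred. The article never says deaths before discharge are left out. The phrase could describe how far the registry search extends, a death registry would also hold in-hospital deaths, and the primary analysis is by intention to treat. The absence of in-hospital death from Table 2 proves little, because that table names no mortality item at all. This stands as far as it goes: the wording is ambiguous, and the verdict is framed accordingly. It does not rescue the definition, because Step 5 shows that the benign reading still leaves a horizon that varies with the stay and is undefined for some patients.

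A second reply is that importance is modest. The Background calls mortality from missed injuries conceivably rare, and the counts above rest on assumed rates. That also stands, and it limits the point to a secondary outcome.

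A third reply is that such detail belongs in an analysis plan. Here, however, the article does state a time origin. The comment is on the origin chosen, not on missing detail.

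Two stronger readings are tempting, and the documents do not support them.

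- **Days off work.** A reader might infer that each bed-day saved reappears as an extra day off work. Table 2 gives only "Proportion of usual days of work or study lost at 1, 6 and 12 months". The interviews are timed from discharge ("Structured interview at 1, 6 and 12 months after hospital discharge"), but nowhere is it stated on which day lost days begin to count. The outcome heading does not settle it, since the same group includes interventions for Type I and II injuries, which arise in hospital by definition. Even if counting began at discharge, the effect would require an unchanged return date that falls inside the window and a usual work or study day.
- **QALYs.** A reader might want these counted from admission too. EQ-5D-5L is first collected one month after discharge, so that would need a utility value for the hospital stay that nobody collects.

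Nor is it a fault that an in-hospital death cannot be a Type III missed injury. That follows from how the primary outcome is defined.

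**Conclusion.** The point holds for mortality only. The protocol anchors mortality to discharge, lists it only among post-discharge outcomes, and names no in-hospital death outcome. On the natural reading, deaths between enrolment and discharge are omitted, and the clock starts at a post-randomisation event the protocol itself expects the intervention to bring forward. The documents do not explicitly exclude these deaths.

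The size cannot be established from the documents. Under assumed in-hospital mortality of 0.5% to 3% after enrolment, about 8 to 48 deaths per 1,595 patients would be lost from the outcome. No between-arm bias has been quantified. The defect is confined to a secondary outcome. It should be corrected because the correction is cheap and the current origin is poor under either reading.

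**What to change.** Replace the mortality definition, in Outcome measures and in Data collection, with: all-cause death from admission to a fixed 12 months after admission, in every enrolled patient whether or not discharged alive. Take deaths during the index admission from the hospital record and later deaths from the Death Registry search. In-hospital death can be reported beside it as a component, so that bed days can be read with deaths in view.

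The cost is small. The change is one of wording and derivation, plus a check that the data collection form (in an additional file not seen here) records vital status and date at the end of the index stay. Hospital records, length of stay and the registry search are already planned. Admission precedes discharge, so 12 months from admission ends no later than the search as now described, which needs only to start at admission. No new patient contact is needed, the interviews can stay timed from discharge, and the primary outcome and sample size are untouched. Recruitment had not begun when the article was written.

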### Outcome measures

The primary outcome is Type III missed (Post-hospital discharge) injury rate. This study aims to compare the effect of a formalised TTS compared to routine care on missed injury rates after hospital discharge (type III).

Secondary outcomes are:Maintenance of intervention effect (comparing two 12-month periods in Group 1)*During Hospital Stay*In-hospital missed injury rate (Type I and II combined)Proportion of TTS performedHospital bed days, ICU bed days*During Follow-up (1,6 and 12 months post hospital discharge)*Clinically significant missed injuries (as determined by expert panel)Interventions required for delayed diagnosis (Type I and II) or missed injuries (Type III)Diagnostic imaging usage (CT, MRI, USS)Predefined complications of care and injury (see above)Readmissions to hospitalDays off workQuality of life (EQ-5D-5 L)Days off workMortality

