This calculation is consistent with a previous study specifically examining the ICC in trauma receiving hospitals. ICC varied depending on outcome, but the average ICC for blunt trauma the ICC was 0.01 [23]. Assuming an average cluster size of 250 patients, this would mean a total of 3,440 patients would require recruitment (approximately 14 clusters) for the primary hypothesis.

The study is adequately powered for the primary hypothesis, and for several secondary outcomes, such as pre- and post-comparison in Group 2, but not for the pre- and post- comparison in Group 1, measuring maintenance of the intervention effect.

De-identified data will be analysed using SPSS v20.0 software (SPPS Inc, Chicago, IL, USA). For continuous variables, we will use an independent *t*-test and chi-square test will be used to compare differences in proportions. All results will be presented with 95% confidence intervals.

Health economic analyses will include a within trial incremental cost-effectiveness evaluation of formal TTS versus standard care. The outcome measure, incremental cost-effectiveness ratio, directly compares the difference in costs between the formal TTS and standard care with the difference in health related quality of life. Health-related quality of life will be measured in quality adjusted life years (QALYs) derived from changes in EQ-5D-5 L measured at multiple time points. A cost-effective threshold of $AUD 50,000 per QALY will be used to determine whether the intervention was cost-effective and a cost-effectiveness acceptability analysis will be conducted using a range of threshold values from $20,000 to $100,000. A 95% confidence interval around the incremental cost-effectiveness ratio will be estimated using bias-adjusted bootstrapping. In addition, sensitivity analyses and sub-group analyses will be conducted to identify the parameters and patient characteristics that affect the likelihood of the intervention being cost-effective. A *P* value of 0.05 or less will be deemed statistically significant.

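### Maintenance of the TTS effect is a no-change hypothesis paired with an underpowered test of difference and no other criterion, so low power favours the hypothesis

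*Protocol article*

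**What the plan says.** Under Aims and hypotheses, the protocol article states: "We further hypothesise that the intervention effect will be maintained". Under Outcome measures, the first secondary outcome is "Maintenance of intervention effect (comparing two 12-month periods in Group 1". Both of those periods are on the formalised TTS, and the entry does not name the variable to be compared.

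Under Statistical analysis and sample size, the method for rates is that a "chi-square test will be used to compare differences in proportions", with the threshold "A *P* value of 0.05 or less will be deemed statistically significant". The same section says that all results will carry 95% confidence intervals. It describes the study as adequately powered for the primary hypothesis and several secondary ones, "but not for the pre- and post- comparison in Group 1, measuring maintenance of the intervention effect".

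The Abstract presents the second 12 months as a way to estimate persistence of the intervention. No margin, retained fraction or other criterion for concluding that the effect was maintained appears.

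**The concern.** For an ordinary superiority outcome, low power counts against the hypothesis. Here the hypothesis is that nothing changes between year 1 and year 2, while the named test looks for a change. The less information there is, the more likely the result agrees with the hypothesis. Disclosing the low power does not tell the reader that a null result cannot support maintenance.

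At stake is what can be concluded from the second 12 months in Group 1 hospitals. The Discussion would have TTS implemented widely if it is effective, so whether an effect outlasts its first year bears on that recommendation. The problem is separate from any calendar-time trend and would remain if there were none.

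**Working it through.** **Inputs from the Statistical analysis and sample size section.** Rates: "we anticipate a decrease in post discharge (Type III) injuries from 14% to 9" per cent. Size: "Using an alpha of 0.05 and a power of 0.80, a sample size of 638 patients per group". Follow-up: "telephone follow-up rate of 40% at 6 months", carried forward to 12 months. ICC: 0.01, from the cited study of trauma-receiving hospitals.

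**Assumptions.** Maintenance is judged on the Type III rate. The four group-periods are of equal size. The loss scenarios are illustrative: half lost is 9% to 11.5%, three quarters lost is 9% to 12.75%, all lost is 9% to 14%.

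**1. The plan's own figure.** Two-sided test, pooled variance, mean rate 0.115:

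n = [1.96√(2×0.115×0.885) + 0.8416√(0.14×0.86 + 0.09×0.91)]² / 0.05² = (0.8843 + 0.3785)² / 0.0025 = 637.9, that is 638. This reproduces exactly.

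638/0.40 = 1,595 recruited per group-period. Four group-periods give 4 × 1,595 = 6,380 recruited and 4 × 638 = 2,552 completers, as stated. Group 1 therefore has 638 completers in each year.

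**2. Chance of a non-significant year-to-year test, independent patients.** Power = Φ[(d − 1.96·SE₀)/SE₁], where SE₀ is the pooled and SE₁ the unpooled standard error at 638 per period.

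| True change | SE₀ | SE₁ | z | Power | Non-significant |
|---|---|---|---|---|---|
| Half lost, 9% to 11.5% | 0.01698 | 0.01697 | −0.488 | 31.3% | 69% |
| Three quarters lost, 9% to 12.75% | 0.01743 | 0.01740 | 0.192 | 57.6% | 42% |
| All lost, 9% to 14% | 0.01786 | 0.01781 | 0.842 | 80.0% | 20% |

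Simulation of the chi-square test agrees (68.6%, 42.1% and 19.6%). For the half loss, the figure varies with follow-up: 75% at 30% follow-up, 62% at 50%, 56% at 60%.

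**3. Allowing for clustering.** Assume 8 hospitals of 80 completers per period (640), ICC 0.01, and a between-period correlation r of hospital effects of 0.5 to 0.8 (r is not in the protocol). The variance of the within-hospital change is multiplied by 1 + 79×0.01 − 80×0.01×r = 1.79 − 0.8r, which is 1.39 at r = 0.5 and 1.15 at r = 0.8. With SE = √{multiplier × [p₁(1−p₁) + p₂(1−p₂)]/640}:

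- Half lost: SE 0.0182 to 0.0200, z = 0.025/SE − 1.96 = −0.58 to −0.71, non-significant 72% to 76%.
- All lost: SE 0.0191 to 0.0210, z = 0.05/SE − 1.96 = 0.66 to 0.43, non-significant 25% to 34%.

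These figures assume a cluster-adjusted analysis. The plain chi-square test gives about 66% to 69% for a half loss (r from 0.5 to 1), because ignoring period-specific hospital variation also produces false positives.

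**4. What the confidence interval can show.** With 9% in both years, SE = √(2×0.09×0.91/638) = 0.0160, so the 95% half-width is 1.96 × 0.0160 = 3.1 points. The chance that the upper limit lies below 2.5 points (half the planned effect) is Φ(0.025/0.0160 − 1.96) = Φ(−0.40), about 35%. For 80% power with that margin, n = (1.96 + 0.8416)² × 2×0.09×0.91 / 0.025², about 2,058 completers per period, or 2,058/0.40 = 5,145 recruited.

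Requiring a significant year-1 reduction as well (9% against 14%, 638 per group), both conditions are met in about 23% of simulated trials. That is below 0.80 × 0.35 = 28%, because a low year-1 rate in Group 1 helps the first condition and hurts the second.

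**The case against.** The strongest reply is that the error is inferred. The article never says that a non-significant test will be taken as maintenance, it speaks of estimating persistence, it promises intervals, and it openly labels this comparison as underpowered. A missing margin for a secondary outcome is also something a condensed article may leave to the full protocol or SAP.

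Much of this stands. A reader might infer that the plan commits itself to reading non-significance as maintenance; the text does not support that. The absence of a margin alone would not be a point either. What remains is what the article does state: a hypothesis of no loss, a generic test of difference and admitted low power. A promised interval helps only if something says how it will be read.

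Two other stronger readings should be set aside:

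- A reader might argue that a TTS that never worked would appear maintained 95% of the time. That figure is simply 1 minus alpha for any two equal rates, and a TTS without effect is the business of the randomised comparison of Group 1 with Group 2, planned at 80% power.
- A reader might conclude that persistence is not tested at all. On the planned numbers with independent patients, a complete loss is detected 80% of the time and a three-quarters loss 58%.

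It is also fair that Outcome measures does not tie maintenance to Type III injury. In-hospital missed injuries and TTS performance come from medical records, available for about 1,595 patients per period, so the figures above do not carry over to them.

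**Conclusion.** The point holds as a low-cost improvement to a secondary outcome; it does not touch the primary comparison. The plan pairs a no-change hypothesis with a test of difference that it calls underpowered and offers no other criterion, so weak data favour the hypothesis. On the Type III rate with 638 independent completers per period, losses of half, three quarters and all of the planned effect would be non-significant about 69%, 42% and 20% of the time. With a cluster-adjusted analysis under the stated assumptions, a half loss gives 72% to 76% and a full loss 25% to 34%. These figures rest on the Type III rate being the variable, on 40% follow-up, on equal group-periods and, for the clustered range, on an assumed between-period correlation.

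**What to change.** In the protocol or SAP, name the variable on which maintenance is judged and assess it by the 95% confidence interval for the year-1-to-year-2 change in Group 1. State that a non-significant test will not be read as maintenance. Claim maintenance only if (a) the randomised year-1 comparison shows a reduction, and (b) the upper 95% limit for the increase lies below a margin the sponsor sets in advance. A margin of 2.5 points is only an illustration; a 5-point margin would have about 88% power at 638 completers per period but equals the whole planned effect. Otherwise, report the estimate and interval as persistence not established.

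This takes two or three sentences and no extra patients or data. The Trial status section says recruitment has not begun, so the rule can be set before any results exist. The cost is that a claim of maintenance becomes hard to reach: with a 2.5-point margin, and under full maintenance of the full planned effect, condition (b) is met about 35% of the time and both conditions about 23%. The plan should say so.
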